## Background

Amputation to the lower extremity is a life-changing event. Approximately two million Americans live with limb loss. An estimated 45% of these amputations are caused by traumatic mechanisms [1, 2]. Once the injury has healed and a prosthetic limb is fitted, the long-term care focuses on maintenance of the prosthesis fit and optimizing physical function [3]. However, even with the use of high-quality prostheses, biomechanical symmetry of gait remains permanently altered [4]. A unilateral transtibial amputation leads to progressive skeletal muscle atrophy in the affected lower extremity [5] and back [6]. The collective effects of asymmetric gait, loss of muscle mass, and reduction of strength increase mechanical stresses at the lumbar spine [4, 7]. These stresses contribute to low back pain (LBP) onset. LBP is a secondary complication in over half of the unilateral amputee population [8–10]. LBP interferes with physical and mental well-being and overall quality of life (QOL) [10].

Long-term care for amputees requires a team of physicians, prostheticians, therapists, and other specialists. Patients often travel long distances to receive their care, and many have resource limitations. Patients may not be able to maintain consistent long-term relationships with therapists or purchase fitness memberships due to financial constraints. Effective home-based interventions that target LBP could minimize travel or cost burden to the patient and substantially impact the secondary disease burden. An exercise mode with strong potential for a home-based intervention is resistance exercise. In the general population, resistance exercise is associated with lower odds of developing LBP [11]. Resistance exercise increases lumbar muscle strength, physical functional, and both physical and mental aspects of QOL [12–17]. The impact and effectiveness of resistance training on chronic LBP severity and pain impact in amputees is not yet known. Moreover, the mechanisms that may contribute to the effectiveness of strength training on LBP relief in amputees are not clear. These evidence gaps are significant barriers to the optimization of care for this special population.

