### Compliance and attrition

Treatment compliance will be assessed by recording the number of completed HBRX training sessions. Participants will be asked to keep an exercise log indicating the exercises performed and RISE and RPE scores for each exercise. Compliance will be defined as completing 85% of all sessions [20]. Members of the study team will be monitoring the exercise performance on a weekly basis. If participants did not remain compliant, their data will not be included in the final analysis. When applicable, participants will be asked for their reasons for poor compliance or dropout. We will collect, assess, and report any spontaneously described adverse events from participants using RedCap data forms. Any unintended or unanticipated adverse events will be reviewed by study physicians for potential medical management. All symptoms will be prospectively followed by phone or in-person until resolution.

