### Primary outcome measures

Pain severity, QOL, and physical functioning are key components in a core outcome set for reporting of clinical studies for LBP [36, 37]. Outcome measures will be collected at our biomechanics laboratory during the subjects two baseline visits (week 0) as well as during the two post-intervention visits (weeks 12–13). Table 2 provides the summary of the study outcome measures.

**Table 2 Tab2:** Summary of outcome measures and participant characteristics. Collected weeks 0–1 (baseline) and 12–13 (post-intervention/wait-list controls)

Primary outcome measures	Data collection instrument or method
Back pain severity	11-point Numerical Pain Rating Scale (NRS_pain_)
	Resting and during activity
Pain impact on quality of life (QOL)	Pain medications used
	Medical Outcomes Short Form-36 (SF-36)
	Oswestry Disability Index (ODI)
	Roland Morris Disability Questionnaire (RMDQ)
Gait kinematics and kinetics	3D motion analysis for temporal spatial parameters of gait and trunk away, bilateral (at self-selected velocity, standard velocity)
	Ground reaction forces
Muscle strength	1-repetition maximum (1-RM) on MedX® clinical Machines: abdominal curl, hip adduction, hip abduction, leg press, and lumbar extension
Muscle morphology	Bilateral B-mode ultrasound measures of muscle thickness and cross-sectional area: multifidus, paraspinals, transversus abdominis, and internal oblique
Step count	StepWatch® monitor, 7-day average count
Participant characteristics	Demographics, weight, Body Mass Index, current medical issues, current medications
	Back pain history
	Pain catastrophizing level (Pain Catastrophizing Scale (PCS))
	Kinesiophobia (11-item Tampa Scale of Kinesiophobia (TSK-11))

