### Kinematics and kinetics of level gait

To assess the effect of HBRX on gait motion, all participants will undergo a 3D gait analysis at baseline and week 12. Upper and lower body kinematic and kinetic data will be collected using a seven-camera, optical motion capture system (Motion Analysis, Inc., Santa Rosa, CA, USA). The camera capture rate will be 120 Hz. Ground reaction forces (GRF) will be collected at 1200 Hz using a force-plated treadmill (AMTI Inc., Watertown, MA, USA) synchronized to the motion capture system. Thirty-three retro-reflective markers will be used to track movement of the body segments from the shoulder to the foot using the marker method of Kadaba et al. [44]. Kinematic data will be processed using Visual 3D software (C-Motion Inc., Rockville, MD, USA). Kinematic variables (joint segment angular velocity, linear velocity, and joint excursion) will be collected from the frontal, sagittal, and transverse planes for ankle, knee, hip, pelvis, shoulder, and elbow. Gait velocity, cadence, step length, vertical displacement of the center of mass, step width, single and double support times, and lateral trunk sway will be calculated. Lateral trunk sway will be calculated using trunk sway in relation to the pelvis [45]. Peak GRF during gait will be calculated and normalized to body weight [46, 47]. Given that GRF and kinematics are velocity-dependent, walking parameters will be collected at two walking velocities, self-selected comfortable velocity and a standard velocity (1.5 m/s) [48]. Data will be expressed as a percentage of the gait cycle.

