### Statistical analysis

Statistical analysis will be performed using the Statistical package for the Social Sciences (SPSS v. 24, IBM Corporation, Armonk, NY, USA). An *α* level will be established at 0.05 a priori for all statistical tests. Data will first be examined for normal distribution using the Kolmogorov-Smirnov test, and skewness and kurtosis parameters. Descriptive statistics will be performed to characterize the participants. Means, standard deviation, and frequencies will be obtained for both study groups. The chi-square test for frequency distributions will be used for demographics, and amputation type. Continuous data that are not normally distributed will be transformed prior to analysis.

The main analysis type that will be used to test the hypotheses of aims 1 and 2 will be a mixed-model, repeated measures approach. These analyses will examine the main effects of the exercise treatment on the study outcomes. The independent variables will include study group (HBRX or CON) and time point (baseline, week 12). Dependent variables will include LBP severity, medication use, perceived impact of LBP on QOL (NRS_pain_, medication number, SF-36, ODI, RMDQ) and biomechanical measures (walking velocity, temporal spatial parameters, GRF, key joint angles). Mixed models are the preferred approach to analyze data with repeated measures; these models account for correlation among repeated measurements, flexible time effects, and handle missing data. To test the hypothesis of aim 3, regression analyses will be used to identify significant contributors to the change in pain over 12 weeks. A hierarchical approach will be used to find the model of best fit. Independent variables that will be entered into the models will include changes in lumbar muscle strength, ultrasound measure of lumbar extensor cross-sectional area, and change scores in SF-36, ODI, and RMDQ. In addition to age, sex, and K-classification, models will be adjusted for other participant characteristics if differences are found from baseline to week 12 (Tampa Scale of Kinesiophobia and Pain Catastrophizing Scale scores, daily step number). Subjects who dropped out or missing participant data will not be included in the final analysis, and intention-to-treat will not be utilized. Due to the relatively small study size, actual treatment effects that would be seen may be washed out during an intention-to-treat analysis.

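### The missing-data exclusion is not limited to the outcome concerned and conflicts with the chosen mixed model; read literally, it discards observed pain scores

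*Protocol article*

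**What the plan says.** The Statistical analysis section closes with this rule: "Subjects who dropped out or missing participant data will not be included in the final analysis". The same sentence rejects an intention-to-treat analysis. The reason given is that, in a small study, such an analysis could dilute the effect of treatment. Earlier in the same section, mixed models are preferred on the ground that "these models account for correlation among repeated measurements, flexible time effects, and handle missing data".

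Compliance and attrition uses the same term for a second exclusion: "If participants did not remain compliant, their data will not be included in the final analysis". Compliance there means completing 85% of sessions.

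The primary outcome is the change in NRS pain, at rest and during activity, from baseline to 3 months. Alongside it, at both time points, the article schedules treadmill gait at a self-selected speed and at 1.5 m/s, five 1-RM tests, ultrasound of several muscles and a 7-day step record. The mixed models for aims 1 and 2 have pain, medication, the quality-of-life questionnaires and the biomechanical measures as dependent variables. Changes in lumbar strength and muscle cross-sectional area are predictors in the aim 3 regression, and step count is a possible covariate there.

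**The concern.** The rule has two faults. First, it does not say which missing item triggers exclusion, or from which model. Someone with a complete pain record and no usable ultrasound image has missing data, and nothing in the sentence keeps that person in the pain analysis. Second, it undoes a stated reason for choosing the mixed model: a method valued for using incomplete records is then given complete records only.

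Bias and precision are both at stake. Entry is open from prosthesis level K2 upward, in people with chronic low back pain. Those who cannot manage the 1.5 m/s walk or a maximal trunk or hip test may well be those with more pain or poorer function. Removing them would select participants on something close to the primary outcome, and in an exercise trial the selection need not be equal in the two groups. This mechanism is reasoned, not documented: the article gives no missingness rates. Any such removals would come on top of dropout, which is all that the enrolment allowance covers.

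**Working it through.** **Reading the rule.** Three features favour exclusion of the whole participant:

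- Values that do not exist cannot enter an analysis anyway, so a rule that leaves them out has content only if it removes people.
- The same sentence removes whole dropouts and rejects intention-to-treat.
- Compliance and attrition uses the term final analysis when it removes the data of a non-compliant participant.

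Against this, the grammar allows the second item to be data rather than persons, and the remark about mixed models points towards keeping incomplete records. The text does not settle the matter.

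**Inputs for the illustration.**

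- From Study population: 16 per group (32 in total), 80% power, alpha 0.05, 25% dropout, 40 enrolled.
- Not stated, so assumed: a two-sided test, the effect size (back-solved below) and all missingness rates.

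**Step 1: the plan's own figure.** By the normal approximation, n per group = 2(1.960 + 0.842)²/d². With d = 1.0 this is 2 × 7.85 = 15.7, rounded up to 16, so 32 in total is consistent with an assumed standardised difference of about 1.0. Solving for exactly 80% power at 16 per group gives d = 0.99 by the normal approximation and d = 1.02 by the two-sample t test. The t-test value is used below.

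**Step 2: the comparator.** 40 × (1 − 0.25) = 30 completers, or 15 per group. Power is the probability that a noncentral t variable with 2n − 2 degrees of freedom and noncentrality d√(n/2) exceeds the two-sided 5% critical value. With n = 15 and d = 1.02 it is about 77%. The fair comparator for this rule is therefore 77%, not 80%.

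**Step 3: further loss from other missing measurements.** The four domains are gait, strength, ultrasound and step count. Fractional group sizes are kept.

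| Assumed further loss among the 30 | Remaining | Power |
|---|---|---|
| None (all pain scores kept) | 30 | about 77% |
| 5% of participants | 28.5 | about 75% |
| 10% of participants | 27 | about 72% |
| Four independent domains at 2%: 1 − 0.98⁴ = 7.8% | 27.7 | about 74% |
| Four independent domains at 5%: 1 − 0.95⁴ = 18.5% | 24.4 | about 68% |
| Four independent domains at 10%: 1 − 0.90⁴ = 34.4% | 19.7 | about 57% |

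If the same people miss every test, a rate of 5% per domain removes only 5% of completers. A 5% rate per domain therefore spans a loss of 5% (complete overlap, 75% power) to 18.5% (independence, 68% power). Overlap is the more plausible direction if pain or poor function is the common cause. Exclusions for non-compliance are not included. The table concerns precision only; the bias cannot be sized from the document.

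**The case against.** The strongest reply is that nowhere does the article say that one missing laboratory measurement removes a pain score. A reader might infer this as the plan's declared rule, but it is an inference from a loosely worded sentence. Exclusion only from the model concerned is also possible. Strength, ultrasound and step data belong mainly to aim 3, and a sensible analyst might confine their absence to that regression. This stands as a limit on certainty. It does not rescue the sentence, because the narrower reading is not written down and an analyst following the words would discard observed primary outcomes.

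A second reply is that the authors gave a reason: in a small trial, intention-to-treat could dilute the effect. That reason concerns people who did not receive or complete the training. It does not bear on someone who trained, attended and reported pain but lacks a gait trial or a scan.

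Three stronger claims are tempting and are not supported:

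- That every self-reported outcome depends on the laboratory visit. The pain scale and questionnaires are scheduled there, but medication use is also self-reported at weeks 4 and 8.
- That the article itself shows travel to be a barrier to study visits. The Background sentence, "Patients often travel long distances to receive their care, and many have resource limitations", is about clinical care. How a missed questionnaire is retrieved is operational detail that an article may leave to the full protocol.
- That the rule cuts power from 80% to 67% or 58% (12 or 10 per group). Those values need 5% or 10% missing independently in each of four domains. Measured from 80%, they also charge this rule with a shortfall already present at 30 completers.

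**Conclusion.** The concern holds in a limited form. The article states an exclusion that is not confined to the outcome concerned and that conflicts with its own reason for using mixed models. Whole-participant removal is the more natural reading but not the only one. On that reading, observed pain scores are lost from the primary analysis, plausibly in a way related to pain or function.

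The loss of power is modest at low missingness, from about 77% to between 75% and 72% for a further 5% to 10% loss, and larger only if gaps are common and scattered across people (about 68% at 18.5%). These values rest on a back-solved d of 1.02, a two-sided test, 25% dropout and assumed missingness. The direction does not depend on them: excluding observed pain scores cannot add information and may add bias.

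**What to change.** In Statistical analysis, replace the exclusion sentence with a rule on these lines: each mixed model includes all randomised participants with any observed data for that outcome; missing gait, strength, ultrasound or step data never removes a participant from the NRS pain analysis; complete predictor data are required only for the aim 3 regression.

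The 85% rule in Compliance and attrition, and the rejection of intention-to-treat, must be reconciled with this wording so that both sections name the same set of participants for the primary analysis. If a compliers-only analysis is wanted, it can be defined separately under its own name.

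The cost is a few sentences in two sections, and the number analysed will differ by outcome and should be reported for each. With only two time points, a participant with a baseline value alone adds little to the treatment comparison, so the main gain comes from keeping those who have both pain scores.

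As an optional and secondary step, week-12 pain scores from participants who cannot attend could be collected remotely. That should be done by a blinded assessor, not by the staff who supervise training, and would need a statement of how the walking-pain rating is obtained.

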## Discussion

This study will examine the efficacy of a 12-week HBRX program on LBP severity and pain impact in persons with traumatic unilateral transtibial amputation. Measurements of key physiological and mechanical factors before and after exercise training relative to changes in LBP severity will help improve our understanding of pain responsiveness to exercise. To date, exercise training trials in amputees to treat secondary musculoskeletal system conditions, such as low back pain, are scarce. Physical activity-related intervention studies in amputees primarily focus on the earlier stages of post-amputation care for gait retraining [60] and gait improvement [61, 62]. The use of resistance exercise to help correct secondary musculoskeletal pain conditions is novel, and fills an unmet care need of transtibial amputees for long-term health and well-being.

The HBRX intervention adheres to the exercise prescription principles of the ACSM [30, 63]. A unique aspect of this intervention is that participants will be able to perform the exercise in their home environment, free of travel or financial restrictions that are common barriers to long-term success with exercise engagement. The use of Skype®, Facetime, and other platforms to monitor training will provide the first evidence of the feasibility of such a program in the greater amputee community. If the outcomes occur as hypothesized, this study could generate a working, functional model of resistance exercise for chronic LBP in lower limb amputees that could be quickly implemented in various clinical environments.

Determining the contribution of exercise-induced changes in mechanical factors, such as gait asymmetries and loading to LBP responsiveness, will be important for optimizing treatments for amputees. Over half of lower limb amputees suffer from chronic LBP [9], but there are not yet protocols in place to help these patients self-manage this pain. Our statistical procedures will help identify the greatest contributors to changes in NRS_pain_ scores from baseline to week 12. Our findings will guide subsequent interventions to maximize the factors that can have the greatest impact on pain severity for this population. There is a chance that anticipated benefits will not be detected in all study outcomes at the conclusion of the study. There is the possibility that pain does not decrease, but function, gait, and QOL improve. An interpretation could be that gait and compensatory motions after amputation are not primary causes of LBP. The improvement of gait symmetry and mechanical loading are still significant benefits for overall functional QOL. Reduction of movement asymmetries can potentially decrease the risk of other secondary musculoskeletal conditions such as osteoarthritis of the lower extremity joints. There is also the possibility that pain decreases over time, but gait symmetry does not. These findings would indicate that: (1) atrophy-related muscle weakness following amputation facilitates the onset of back pain, and strengthening these muscles is an important therapeutic goal and (2) asymmetrical movement may not be the primary cause of LBP development in amputees. According to prior work, the expected decrease in back pain from resistance exercise will be beneficial for subsequent reduction of back pain-related disability [20], reduction of pain catastrophizing [20], improvement in QOL [21] and increase in steps per day [54]. An opportunity then arises for further research to identify what different types and intensity of exercises may improve gait in lower extremity amputees.

Strengths of the study include a single-assessor-blinded, randomized controlled design. The main study outcomes will be assessed at baseline and at week 12. The outcomes include a combination of objective and subjective measures to capture the exercise adaptations and the patient experience. Objective measures include biomechanical gait parameters, muscle morphology, muscle strength, and daily step count. Subjective, patient-reported outcomes will include pain and its impact on overall QOL. The instruments and tests that will be administered are well-accepted, valid, reliable and sensitive to change [38, 42, 43]. Exercise benefits will be offered to all enrolled participants; the CON group will wait the 12 weeks before beginning the training.

In summary, the findings from this study will help to determine whether a HBRX program for unilateral transtibial amputees with chronic LBP can decrease pain severity and positively impact several physiological and mechanical factors that contribute to LBP. After adjusting for participant characteristics, our analyses will determine the relative contribution of these exercise-induced changes in these factors on pain responsiveness in this population. Future trials can be designed to target the factors we identify here as effective in reducing LBP.

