The aims of this study are to determine whether home-based resistance exercise (HBRX) among unilateral transtibial amputees with LBP can reduce LBP severity and its impact on QOL and improve the biomechanical symmetry of gait. The relative contribution of key factors that predict pain responsiveness with HBRX will be determined. The research hypotheses are as follows: (1) HBRX will reduce subjective pain ratings, pain medication use, and the impact of pain on QOL; (2) HBRX will reduce gait asymmetries and increase gait velocity; and (3) HBRX-induced changes in lumbar muscle strength, lumbar muscle cross-sectional area, and perceived QOL will predict pain responsiveness for LBP in unilateral transtibial amputees.

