### Study population

A total of 40 transtibial amputees aged between 18 and 65 years will be recruited for this study. Participants will be recruited from a major regional prosthetics center and from the greater north Florida community via relationships with local prosthetic clinics and amputee support groups. Study flyers, social media posts, and online web advertisements will also be used. Participants will be eligible if they meet the following inclusion and exclusion criteria. Inclusion criteria: men or women aged 18–60 years, traumatic transtibial amputation more than 1 year prior to enrollment, current prosthesis worn for at least 6 months, suffering from chronic LBP (>3 months with at least three pain episodes per week), must have regular access to a computer for Skype®, or a mobile phone or iPAD to perform Facetime; prosthesis K-level of K2 or greater (indicating the subject is able to ambulate and traverse low-level environmental barriers such as curbs, stairs, or uneven surfaces) [20]. Exclusion criteria: dysvascular amputation, acute back injury, pregnancy, any other chronic back pathology (i.e., herniated disc, ankylosing spondylosis, other related neurological disease), pain symptoms or functional limitations (including those that may require assistive devices) that preclude participation in resistance exercise or physical activity, back surgery within the past 2 years that restricts daily physical activities, and currently enrolled in any other resistance or strengthening exercise interventions. Written informed consent will be obtained from each participant.

The primary outcome of the study is the Numerical Pain Rating Scale (NRS_pain_) value for LBP. Sample size estimation indicated that a total sample size of 32 was necessary to detect clinically meaningful differences in NRS_pain_ from baseline to week 12. Based on published evidence of comparative studies of resistance exercise and controls on LBP [21], a sample size of 16 per group will yield a power of 80% at an *α* value of 0.05. To account for the anticipated dropout rate of 25%, the enrollment target will be 40.

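### The Discussion draws a conclusion about the onset of back pain that this trial cannot support, and the asymmetry hypothesis has no between-limb variable among those listed

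*Protocol article*

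**What the plan says.** The Discussion considers several possible result patterns. One reads: "There is also the possibility that pain decreases over time, but gait symmetry does not". Two conclusions follow from it. The first is stated flatly: "These findings would indicate that: (1) atrophy-related muscle weakness following amputation facilitates the onset of back pain". The second is cautious: "asymmetrical movement may not be the primary cause of LBP development in amputees".

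Study population restricts entry to people "suffering from chronic LBP (>3 months with at least three pain episodes per week", among other criteria. The same section bases the sample size on pain alone: "a total sample size of 32 was necessary to detect clinically meaningful differences in NRS_pain_ from baseline to week 12". That is 16 per group, with 80% power at an α of 0.05 and 40 enrolled to allow for 25% dropout.

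The second hypothesis, at the end of Background, is that "HBRX will reduce gait asymmetries and increase gait velocity". The gait outcomes named in Statistical analysis are "biomechanical measures (walking velocity, temporal spatial parameters, GRF, key joint angles". Kinematics and kinetics of level gait lists the quantities to be calculated: velocity, cadence, step length and width, support times, centre-of-mass displacement, lateral trunk sway and peak ground reaction force. Table 2 records that motion capture is bilateral, at a self-selected and a standard velocity.

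**The concern.** There are two linked problems.

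The first is the inference. Relief of established pain under an exercise programme does not show what started the pain. The stated trigger also needs only a fall in pain and no change in gait symmetry. It does not require that muscle strength or size changed, or that the fall was larger in HBRX than in CON. Weakness is reached by eliminating gait, and the elimination rests on an outcome for which the trial was not sized.

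The second is the measurement. A hypothesis about asymmetry needs a comparison of the prosthetic with the intact limb. Step length or ground reaction force can change in both limbs together and leave asymmetry where it was, so analysing the listed variables as they stand would not test the hypothesis.

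Pain improving while gait is non-significant is a plausible result here even if symmetry truly improves. Under the present text it would be written up as evidence on the cause of back pain, and aim 2 could be answered with variables that do not measure asymmetry.

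**Working it through.** **Onset claim (no arithmetic).** Set the entry criterion beside the conclusion. Every participant has had low back pain for more than 3 months at baseline, so the trial contains no transition from no pain to pain. Its outcome is change in the severity of existing pain. More participants would estimate that change more precisely but would add no information on onset.

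The listed aim 3 predictors (changes in lumbar strength, lumbar extensor cross-sectional area, SF-36, ODI and RMDQ) include no gait variable either. That regression, as listed, cannot weigh gait against muscle.

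**What a null gait result can show.**

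Inputs from Study population: 16 per group, 80% power, α = 0.05, 40 enrolled, 25% dropout. Assumptions: a two-sided test (sidedness is not stated) and effects in SD units, because the article gives no SD or target difference for gait.

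1. *The plan's own figure.* The 16 per group cannot be reproduced forward, because no effect size or SD for pain is given. Solving backwards, d = (1.960 + 0.842) × √(2/16) = 0.99 SD; the exact t test gives 1.02 SD.
2. *Number available.* The plan targets 16 per arm. Taking 25% off 40 leaves 40 × 0.75 = 30, or 15 per arm. Both are used below.
3. *Detectable difference at 80% power (t test).* 1.02 SD at 16 per arm; 1.06 SD at 15.
4. *95% CI half-width.* t(0.975, 2n − 2) × √(2/n). At 16: 2.042 × 0.354 = 0.72 SD. At 15: 2.048 × 0.365 = 0.75 SD.
5. *Power by true difference (t test, unadjusted).*

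| True difference | 16 per arm | 15 per arm |
|---|---|---|
| 0.3 SD | 13% | 12% (12.5%) |
| 0.5 SD | 28% | 26% |
| 0.8 SD | 59% | 56% |
| 1.0 SD | 78% | 75% |

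A true 0.5 SD change is therefore missed 72% of the time at 16 per arm and 74% at 15.

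6. *With baseline adjustment.* The effective d is 0.5/√(1 − r²). For r = 0.5 this is 0.58, with power 35% at 16 per arm. For r = 0.7 it is 0.70, with power 48%. The change is still missed 65% to 52% of the time.
7. *What would be needed.* 80% power at 0.5 SD takes about 64 per arm. Showing equivalence within ±0.5 SD (two one-sided tests at 0.05, 80% power) takes 2 × ((1.645 + 1.282)/0.5)² ≈ 69 per arm.

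**Symmetry variable.** Hypothesis 2 names asymmetry and the Discussion interprets gait symmetry. Neither the calculated gait quantities nor the dependent variables include a between-limb ratio, difference or index. The bilateral capture in Table 2 means one could be derived from data already planned.

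**The case against.** The text is Discussion prose about hypothetical results, not an analysis or decision rule. A reader might infer that the protocol commits to causal conclusions from a null gait result. It does not go that far. Only the onset clause is flat, and the clause resting most directly on the null gait result is hedged. That stands.

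A reader might also add the sentence "An interpretation could be that gait and compensatory motions after amputation are not primary causes of LBP" as a further example. It belongs to the opposite scenario, where pain does not fall but gait improves. The null there is on pain, the outcome that was sized, so the gait-power argument does not reach it. It is also hedged.

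A third tempting reading is that the trial is too small for the onset claim. That misplaces the fault, because size bears only on the hedged clause.

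Nor do the words about change over time replace the planned comparison. Statistical analysis includes both study group and time point in the mixed model, so the fault is loose wording of the trigger.

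On symmetry, the article gives categories of variable, and a condensed article may leave an index formula to the full protocol. It does not say that raw values will be tested in place of symmetry. So this is under-specification, not contradiction. It remains that the hypothesis turns on asymmetry and nothing listed, as written, measures it.

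Finally, the power figures depend on assumed effect sizes and correlations. Baseline adjustment helps, but at the correlations assumed it does not make a null result informative about a 0.5 SD change.

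**Conclusion.** The point holds in three parts.

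- **The onset conclusion is invalid by design**, whatever the sample size. This rests only on the entry criterion and the wording of the trigger.
- **The hedged reading about asymmetry would rest on weak evidence.** The trial has 80% power only for about 1 SD, and a non-significant result has a 95% CI reaching about 0.72 to 0.75 SD either side of the estimate (unadjusted). A 0.5 SD change would be missed about 72 to 74% of the time unadjusted, or about 52 to 65% at 16 per arm with adjustment. These figures assume a two-sided 0.05 test and a baseline correlation of 0.5 to 0.7 for the adjusted case. The article gives no gait SD or meaningful change to replace the standardized effects.
- **No between-limb measure is named for hypothesis 2**, although the data for one will be collected. The full protocol may define it.

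None of this touches the primary pain analysis. It should be corrected because it governs how a plausible result would be interpreted and whether aim 2 is answered at all.

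**What to change.** 1. Delete the inference about onset from the Discussion.
2. State that a non-significant gait result will be reported as an HBRX-CON difference with its 95% CI and will not be read as absence of change. Word the scenario itself as a between-arm contrast.
3. Define the aim 2 asymmetry variables as prosthetic-versus-intact indices derived from the bilateral data, for example step length, single-support time and peak ground reaction force at the standard velocity. Keep self-selected gait velocity for the other half of hypothesis 2. If the full protocol already defines such indices, name them in the list of dependent variables.

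The cost is a few sentences and a small amount of derived-variable work, with no new data collection. Recruitment was still open when the article was submitted. The downside is a weaker mechanistic statement.
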